## 2. Materials and Methods

### 2.1. Study Design

This is a prospective, multicenter observational protocol, spanning 24 months, across 22 hospitals affiliated with the Lombardy Cardiac Arrest Registry (“Lombardia CARe”—a full list of the hospitals is provided in Table 1). This network covers a population of approximately 4.3 million people and includes densely populated urban areas and sparsely populated rural and mountainous locations.

In the REVIVE project, each of the 22 hospitals will have a named contact person (usually a senior cardiologist) who will enroll eligible survivors and inform the study team of the clinical status and readiness to be assessed before hospital discharge. Based on registry data from 2022, >90% of patients with a good neurological outcome (CPC 1–2; mRS ≤ 3) were discharged from 11 hospitals affiliated to this network, therefore these sites have been highlighted in Table 1 as ‘Main Recruiters’ and a picture describing their approximate location in the Lombardy region is provided (Figure 1).

The REVIVE project plans to enroll consecutive OHCA survivors meeting eligibility criteria and to follow them up for 12 months post-discharge. Survivors will be assessed at five different timepoints: **T0**—before discharge (or within 15 days post-discharge); **T1**: 1 month post-discharge; **T2**: 3 months post-discharge; **T3**: 6 months post-discharge; **T4**: 12 months post-discharge.

At each time point, the same battery of questionnaires will be administered **in-person or over the telephone/via telemedicine**, based on patient preference and feasibility.

Should a significant need be identified, the study team will, in the first instance, consider whether psychological therapy/cognitive rehabilitation can be provided in-house; however, it is expected that most patients will be referred to community-based rehabilitation programmes or other specialists where required.

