### 2.4. Statistical Methods

Baseline characteristics will be reported as means ± SD, or medians [IQR] for continuous variables, and as frequencies (%) for categorical variables. Prevalence of psychological distress, cognitive impairment, fatigue, symptoms of post-traumatic stress, and reduced quality of life will be estimated at all timepoints; exact 95% confidence intervals will be calculated. Reduced quality of life will be defined as an EQ-5D-5L VAS score at least 7 points lower than the age-matched Italian general population mean [26], based on established minimal clinically important differences identified in chronic disease populations [27,28].

Incidence rates (expressed per 100 person-years) for mood disorders, post-traumatic stress symptoms, reduced quality of life, and cognitive impairment will be calculated for participants free of the respective condition at baseline. Incident cases will be defined as follows: a HADS subscale score > 8 for mood disorders (either anxiety or depression subscale), IES-R ≥ 33 for post-traumatic stress symptoms, a MoCA score < 26 for cognitive impairment, and a decrease of ≥7 points from the age-matched normative mean on the EQ-5D-5L VAS for reduced quality of life. Baseline status will be determined using the initial T0 assessment; if T0 data are missing, the T1 (1-month) assessment will be used. Participants with missing data at both T0 and T1 for a given outcome will be excluded from the incidence rate calculation for that outcome. Incidence rates will be reported with exact 95% confidence intervals.

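### One score beyond a cut-off after one negative baseline counts as an incident case, so the incidence rates will mix score fluctuation with new disorder

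*Protocol article*

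**What the plan says.** All of this is in the Protocol article.

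- **Risk set (2.4).** Incidence rates per 100 person-years "will be calculated for participants free of the respective condition at baseline".
- **Baseline (2.4).** Freedom from the condition is judged on one assessment: "Baseline status will be determined using the initial T0 assessment; if T0 data are missing, the T1 (1-month) assessment will be used".
- **Event (2.4).** For mood: "Incident cases will be defined as follows: a HADS subscale score > 8 for mood disorders (either anxiety or depression subscale". For the next two outcomes: "IES-R ≥ 33 for post-traumatic stress symptoms, a MoCA score < 26 for cognitive impairment". For quality of life: "a decrease of ≥7 points from the age-matched normative mean on the EQ-5D-5L VAS for reduced quality of life". This last is a distance from the population norm, not from the patient's own baseline.
- **Schedule (2.1).** "Survivors will be assessed at five different timepoints", namely T0 and then 1, 3, 6 and 12 months after discharge. "At each time point, the same battery of questionnaires will be administered".

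The section does not write out that a crossing at any follow-up counts, but a person-time rate over T1 to T4 implies it. No confirming assessment, minimum worsening or diagnostic interview is asked for.

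**The concern.** Every one of these scales has retest error. The rule selects patients who fall on the healthy side of a line on one reading and then counts the first time a later reading falls on the other side. A patient with MoCA 26 at T0 and 25 at T1 is a new case of cognitive impairment even if all later scores are 27. HADS 8 then 9, or an EQ VAS that moves from 6 to 7 points below the norm, also counts. For mood there are 4 × 2 = 8 readings on which to cross, because either subscale suffices. Within the incidence calculation the movement is one-sided: patients positive at T0 who later become negative never enter it.

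At stake is how the rates are read. If they are reported as mood disorder, post-traumatic stress symptoms or cognitive impairment arising after discharge, they will overstate new onset by an amount that readers cannot judge from the rate itself. The exact confidence intervals reflect sampling error only. Parallel MoCA forms address practice effects, not random crossing. The comparison of complete-case and imputed data applies the same rule twice.

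**Working it through.** **No figure to reproduce.** The plan states no expected incidence. Its planning prevalences serve as anchors: 25% anxiety or depression at 6 months (section 3.2) and 40–50% cognitive impairment at 6 months (Introduction).

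**Model.** Score at visit j = stable true level + independent visit error. Reliability r is the share of variance due to the true level. Visits fall at 0, 1, 3, 6 and 12 months, with 400,000 simulated patients per scenario. Quantity of interest: P(at least one of the four follow-up scores beyond the cut-off, given T0 not beyond it). Rate = 100 × cases ÷ person-years to first crossing or month 12.

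**Inputs from the plan.** The cut-offs (MoCA < 26, HADS subscale > 8 on either, IES-R ≥ 33) and the visit times.

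**Assumed inputs (the article gives none).** r = 0.7 to 0.9; MoCA mean 26, SD 3 (about 43% impaired at T0); HADS subscales mean 5, SD 3.8, correlation of true levels 0.6; IES-R mean 20, SD 16. Recovery by month 3: MoCA up 1 point, HADS down 0.5 SD (0.5 × 3.8 = 1.9 points), IES-R down 8 points.

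**Retest error for MoCA.** Standard error of one score = SD × √(1 − r): 3 × √0.1 = 0.95 to 3 × √0.3 = 1.64. For a difference of two scores, multiply by √2: 1.34 to 2.32 points. A fall from 26 to 25 is smaller than one standard error of a difference.

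**Results, nobody truly worsening** (ranges run from r = 0.9 to r = 0.7):

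| Scale | Counted as incident, stable | Counted as incident, recovering |
|---|---|---|
| MoCA | 26–46% (32–69 per 100 person-years) | 13–32% |
| HADS, either subscale | 19–34% | 6–17% (6–19 per 100 person-years) |
| IES-R | 15–28% | 5–14% (5–15 per 100 person-years) |

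EQ VAS was not simulated.

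**Second check, anchored to the plan's prevalences.** With cut-offs set to give 25% (mood) and 45% (MoCA) positive at T0, stable scores give 17–31% and 27–47%. With slower recovery (0.5 SD by 12 months) they give 6–16% and 11–29%. In numbers for mood: 280 × 0.75 = 210 at risk, so 210 × 0.17 ≈ 36 to 210 × 0.31 ≈ 65 counted cases with no true change if scores are stable. Some of the crossings (about a third for MoCA, stable) are patients whose true level was already beyond the cut-off but who were missed at T0. They are not new disorder either.

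**Effect of requiring two consecutive positives, nobody worsening.** Stable: MoCA 11–19%, HADS 7–12%, IES-R 5–9%. Recovering, second check: MoCA 2–8%, HADS 1–3%. Confirmation reduces the problem but does not remove it.

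**Share of cases.** The runs above contain no true onset, so they cannot say what fraction of reported cases is spurious. If 10% true onset (+2 SD) is added as a further assumption, 38–82% of counted cases have no true onset, across both scales and both courses.

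**The case against.** Several points on the other side stand.

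- **Incidence is not an aim.** The Abstract and Introduction name feasibility, acceptability and prevalence. No threshold or sample size depends on incidence.
- **Other outputs show the net course.** Prevalence at every visit sets improvers against decliners, and the mixed models use the scores themselves. If nobody worsens, both will look flat or improving beside the incidence rates. A reader might infer that the study as a whole will misstate recovery; the article does not support that.
- **Transient is not false.** A raised HADS score at 3 months that resolves by 6 months can be a real episode. First crossing among those free at baseline is a usual incidence definition, and requiring persistence estimates something else. The Study Design section also foresees therapy or referral for patients with significant need, so a true case may be negative at the next visit because it was treated.
- **The size is assumption-driven.** Correlated visit errors or attrition (the plan accepts 50% retention) would lower the counts, and patients with T1 as baseline have only three follow-ups. With recovery and a very reliable scale the figure falls to about 5–6%.

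These points limit the consequence and rule out simply replacing the definition. They do not remove the inflation: no other passage corrects the incidence rates, and the rule is fixed in the article itself, so it has not been left to an analysis plan.

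**Conclusion.** The point holds for the incidence rates and only for them. With imperfect reliability and a one-visit baseline, some patients without true change must be counted. Under the stated assumptions that is roughly 15–46% of baseline-free patients across the three scales if scores are stable, and 5–32% if patients recover.

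Two stronger readings are not supported. A reader might infer that much or most of the reported incidence will be noise. That depends on true onset, which the documents do not give, and the 38–82% above needs an assumed 10%. A reader might also quote much higher MoCA figures: a mean of 24.5 instead of 26 yields up to 61%, or 111 per 100 person-years. That input makes about 63% impaired at T0, against the 40–50% at 6 months in the Introduction.

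The change is worth making because it is cheap and stops the rate being read as new disorder.

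**What to change.** In section 2.4, keep the planned rate but label it *first positive screen*. Report two pre-specified figures beside it:

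1. A rate of confirmed cases: free at baseline, then beyond the cut-off at two consecutive assessments, dated at the first. First positives at T4, or without a next assessment, are shown separately as unconfirmed.
2. The proportion moving from positive to negative over the same intervals.

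Add that the single-crossing rate is not to be interpreted alone as new disorder.

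Cost: a little more analysis on data already collected, and a stated rule for missed confirming visits. The confirmed rate misses episodes that resolve or are treated before the next visit, and between T3 and T4 it demands six months' persistence. It is therefore a companion figure and not a replacement.

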#### 2.1.3. Enrolment and Assessments

The Lombardia CARe Registry records all admissions of patients who have suffered an out-of-hospital cardiac arrest across seven provinces in the Lombardy region, updated to the previous 24 h. This registry is monitored daily by the team involved in this study; for patients admitted to the IRCCS Policlinico San Matteo Hospital in Pavia, their clinical history (including survival and neurological status) is monitored via the hospital internal electronic system and, if eligible, they are approached to provide consent for participation to this study close to their discharge day, usually in the cardiology ward. For those patients admitted to one of the ten other main recruiting hospitals (Figure 1), the local investigator will approach them for screening and enrollment. They will also inform the study team about their clinical status and readiness for assessment before hospital discharge. To minimize the risk of patients being missed, an email will be sent to all the investigators of the main recruiting hospitals every Monday and every Friday. The secondary recruiting centres do not have an allocated local investigator, so they will be contacted as and when required.

Most eligible patients are supposed to be approached before hospital discharge; if not, the study management team will contact them within 15 days post-discharge. Following informed consent, baseline assessment will be conducted by a clinical psychologist, either in-person (for patient admitted to Fondazione IRCSS San Matteo hospital, Pavia) or remotely (via telephone call or telemedicine, for all other patients), using measures of cognitive ability (Montreal Cognitive Assessment [22]), anxiety and depression [23], health-related quality of life [24], and symptoms of post-traumatic stress disorder [25]. Parallel versions of the cognitive assessment will be administered to reduce practice effects. A list of all measures and their purpose is described in Table 2.

In addition to quantitative instruments, starting from the first follow-up after hospital discharge (that is, the 1-month follow-up), patients will also undergo a brief semi-structured, qualitative interview focused on their own subjective experience of returning to day-to-day life, fatigue, cognitive problems, mood difficulties, and their ability to access appropriate information/support about their condition (Appendix A; Table A1).

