## Figures and Tables

**Figure 1 jcm-14-03631-f001:**
[figure not shown]
Location of the recruiting hospitals in the Lombardy region. Different colors identify the different provinces.

**Table 1 jcm-14-03631-t001:** Hospitals participating in the *Lombardia CARe Cardiac Arrest Registry*, categorized into *Main Recruiters* and *Secondary Recruiters* in the REVIVE study.

[figure not shown]	
Main Recruiters	Secondary Recruiters
**Fondazione IRCCS Policlinico San Matteo, Pavia**	ASST Valle Olona—Ospedale di Gallarate, Gallarate
**ASST dei Sette Laghi** **Ospedale di Circolo e Fondazione Macchi, Varese**	ASST di Mantova—Ospedale di Asola, Castiglione delle Stiviere
ASST di Mantova—Ospedale Carlo Poma, Mantova	Ospedale Sacra Famiglia Fatebenefratelli, Erba
ASST Spedali Civili di Brescia—Presidio Spedali Civili, Brescia	ASST di Lecco—Ospedale Alessandro Manzoni, Lecco
**ASST Lariana—Ospedale Sant’Anna, Como**	Ospedale Valduce, Como
**ASST di Lodi—Ospedale Maggiore, Lodi**	Ospedale Moriggia-Pelascini, Gravedona
**Fondazione Poliambulanza Istituto Ospedaliero, Brescia**	ASST Papa Giovanni XXIII—Ospedale Papa Giovanni XXIII, Bergamo
**ASST Ovest Milanese—Ospedale Civile, Legnano**	ASST Valle Olona—Ospedale di Busto Arsizio, Busto Arsizio
**ASST di Crema—Ospedale Maggiore, Crema**	ASST dei Sette Laghi—Ospedale di Cittiglio, Cittiglio
ASST di Cremona—Ospedale di Cremona, Cremona	ASST Valtellina e Alto Lario—Ospedale Civile, Sondrio
Humanitas Mater Domini, Castellanza	ASST Lariana—Ospedale Sant’Antonio Abate, Cantù
**Ospedale di Manerbio, ASST Garda, Manerbio, Brescia, Italy**	ASST dei Sette Laghi—Ospedale di Tradate, Tradate
**Ospedale di Chiari, ASST Franciacorta, Chiari, Brescia, Italy**	ASST di Pavia—Ospedale Civile, Vigevano
	Ospedale Erba-Renaldi, Menaggio
	Humanitas Research Hospital, Milano
	ASST di Pavia—Ospedale di Varzi, Varzi
	ASST Melegnano e Martesana—Ospedale di Melegnano, Melegnano
	ASST di Mantova—Ospedale di Pieve di Coriano, Pieve di Coriano
	ASST di Pavia—Ospedale Civile, Voghera

**Table 2 jcm-14-03631-t002:** Key assessment tools used for evaluating cognitive function, psychological distress, and health-related quality of life.

Assessment Tool	Purpose
Montreal Cognitive Assessment (MoCA)	Screens for cognitive deficits in memory, executive functions, visuospatial abilities, attention, language, and orientation.

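### One MoCA cut-off (<26) covers in-person, video and telephone testing, although visual items cannot be given by voice call, so impairment may be misclassified in patients tested by telephone

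*Protocol article*

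**What the plan says.** **Mode.** Under Section 2.1, at each of T0 to T4 "the same battery of questionnaires will be administered", either "in-person or over the telephone/via telemedicine", with the choice "based on patient preference and feasibility". Section 2.1.3 ties baseline mode to the hospital: in person at the coordinating centre, and otherwise "remotely (via telephone call or telemedicine, for all other patients), using measures of cognitive ability". The MoCA is the cognitive measure named there.

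**Content.** Table 2 gives the MoCA's purpose: "Screens for cognitive deficits in memory, executive functions, visuospatial abilities, attention, language, and orientation".

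**Case definition.** Section 2.4 counts an incident case by "a MoCA score < 26 for cognitive impairment". The definition is written for incident cases. No separate definition is given for prevalence, and Table 2 gives no MoCA threshold.

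**Control of versions.** The only statement is in Section 2.1.3: "Parallel versions of the cognitive assessment will be administered to reduce practice effects". It deals with repetition, not with mode.

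**Use of mode in the analysis.** Sections 2.2 and 2.4 compare remote with face-to-face patients on recruitment and on attrition or retention. For MoCA change from T0 to T4, Section 2.4 gives age, sex and comorbidities as examples of covariates and does not name mode.

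**The concern.** A patient on a voice call cannot see a figure or have a drawing scored. Taken together, Sections 2.1, 2.1.3 and 2.4 and Table 2 call for one battery with visual content, permit a medium that cannot carry that content, and judge the result against one total-score limit. Points that could not be earned would then count as impairment.

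The error would not be uniform. At baseline it falls only on patients outside the coordinating hospital, so it is confounded with site. Afterwards it follows patient preference, so a change of mode between visits can look like decline or recovery.

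Prevalence of cognitive impairment is part of aim (b) in the Introduction. The incidence rate and the longitudinal MoCA model depend on the same scores.

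**Working it through.** **Yardstick from the plan.** The article gives no figure for MoCA error, so I first checked its precision statement (Section 3.2: 25% prevalence, 5% precision, 95% confidence, about 280 patients).
- n = z²p(1−p)/d² = 1.96² × 0.25 × 0.75 / 0.05² = 288.1. At n = 280 the half-width is 5.07 points, in line with the stated 5%.
- In the 0.05 column of Table A2, the entries 255, 329, 372 and 384 (proportions 0.21, 0.31, 0.41, 0.51) all reproduce.
- The Introduction puts cognitive impairment at 40–50% at 6 months. At n = 280 the half-width is then 1.96 × √(0.40 × 0.60/280) = 5.7 points, or 1.96 × √(0.50 × 0.50/280) = 5.9 points.

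**Illustration of the bias.** The following are assumptions, not document figures:
- MoCA scores are roughly normal with SD 3 to 4.
- k points cannot be earned by voice call and are not replaced.
- A share f of the cohort is tested by voice call.
- True prevalence p0 is the same in every mode.

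Rate in telephone-tested patients: p1 = Φ(Φ⁻¹(p0) + k/SD). Pooled rate: (1−f)·p0 + f·p1.

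For p0 = 40%, Φ⁻¹(0.40) = −0.253. With k = 1 and SD = 3, p1 = Φ(−0.253 + 0.333) = 53.2%, and at f = 0.5 the pooled rate is 0.5 × 40 + 0.5 × 53.2 = 46.6%.

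| k | SD | Telephone-tested | Pooled, f = 0.25 | Pooled, f = 0.50 | Pooled, f = 0.75 |
|---|---|---|---|---|---|
| 1 | 4 | 49.9% | 42.5% | 44.9% | 47.4% |
| 1 | 3 | 53.2% | 43.3% | 46.6% | 49.9% |
| 2 | 4 | 59.7% | 44.9% | 49.9% | 54.8% |
| 2 | 3 | 66.0% | 46.5% | 53.0% | 59.5% |

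At f = 0.50 the pooled rate rises by 4.9 to 6.6 points for one lost point and by 9.9 to 13.0 for two. Starting from p0 = 50%, the telephone-tested rate becomes 59.9–63.1% (k = 1) or 69.1–74.8% (k = 2), and the pooled rise at f = 0.50 is 4.9 to 6.5 or 9.6 to 12.4 points.

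These are approximate upper figures for each k. The formula takes k points from everyone, but a patient who would have failed some of those items in person loses fewer.

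**Incidence.** Two effects oppose each other. A patient tested in person at T0 and by telephone later may fall below 26 through the lost points alone and be counted as an incident case. A patient tested by telephone at T0 may be wrongly classed as impaired and leave the at-risk set, which Section 2.4 limits to those without the condition at baseline. The net direction cannot be settled from the article.

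**The case against.** The best reply is that this is a condensed article. The MoCA form and scoring rule for telephone use may be in a full protocol that is not shown, and a clinical psychologist administers the tests. That stands in part: a reader might infer that impairment will certainly be overstated, and the article does not establish this. Prorating the items that can be given would remove most of the shift, and nothing rules that out. But what is printed is more than silence. It fixes one battery for all modes and one limit, and it addresses MoCA versions for practice effects only.

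Other stronger readings also fail:
- **All remote patients are affected.** Section 2.1.3 allows telephone or telemedicine. If telemedicine means video, visual items may be possible. The voice-call share is unknown and could be small.
- **No telephone patient could reach 26.** This needs a 30-point scale and at least five lost points scored as zero (30 − 5 = 25). The article gives neither figure.
- **Every switch to telephone makes an incident case.** This happens only when the lost points carry that patient below 26.
- **The MoCA model excludes mode.** The covariate list is open, and hospital random effects may absorb part of a mean shift. They do not correct a classification at a threshold or a switch within a patient. Neither does multiple imputation with hospital ID.
- **The study's main criteria are undermined.** The feasibility and acceptability thresholds (Section 2.2) and the precision statement (Section 3.2) do not use the MoCA. HADS, IES-R and EQ VAS definitions are untouched.

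**Conclusion.** The concern holds for MoCA tests given by voice call. Followed as written, the plan can misclassify these patients and can let a change of mode pass for a change in cognition. Upward bias in prevalence depends on items not given scoring zero, or on a shortened form keeping <26. Use of <26 for prevalence is itself an inference, though the only one the text offers.

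Under the stated assumptions, one lost point with half the cohort tested by telephone shifts pooled prevalence by about as much as the sampling half-width, and two points by roughly twice that. A larger sample would not reduce this. The point should be fixed, but it affects one of several outcomes under aim (b) and does not threaten the study as a whole.

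**What to change.** 1. For voice calls, specify a MoCA form without visual items, with its own pre-specified cut-off. Apply the full MoCA and <26 only in person or by video.
2. State that the cut-offs apply to prevalence as well as incidence.
3. Record mode (in person, video, voice) and form at every visit. The planned retention comparison already needs the remote versus face-to-face split, so the additions are voice versus video and the form used.
4. Count incident cognitive impairment only between visits with comparable forms.
5. Include mode as a time-varying covariate in the longitudinal MoCA model.
6. Report prevalence of cognitive impairment by mode.

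The cost is protocol wording, two REDCap fields and some analysis work. The drawback is two forms and two cut-offs, with fewer directly comparable scores. Recording should start early, because visit-level mode may not be recoverable afterwards.

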Longitudinal changes in HADS, MoCA, EQ-5D-5L, and IES-R from T0 to T4, as well as differences in the retention rate between patients seen remotely or face-to-face, will be analyzed using mixed-effects models (linear or logistic) incorporating time and potential covariates (e.g., age, sex, comorbidities). Models will initially include random intercepts and slopes at participant and hospital levels. Different residual covariance structures (e.g., first-order autoregressive [AR(1)]) will also be explored. Model selection will be guided by the Akaike Information Criterion (AIC) and Bayesian Information Criterion (BIC); simpler random intercept-only models will be adopted if convergence issues arise. Missing data will be handled using Multiple Imputation by Chained Equations (MICE), assuming a Missing At Random (MAR) mechanism. Twenty imputed datasets will be generated, incorporating all key predictors and outcomes, as well as hospital ID. Participants who completely withdraw from this study will be treated as censored at their last observation without further imputation. Sensitivity analyses comparing complete-case and imputed datasets will be conducted to assess the robustness of the findings. A *p*-value < 0.05 (two-sided) will denote statistical significance.

Qualitative data will be derived from detailed notes taken during semi-structured interviews; the analysis will employ a framework approach, well-suited for applied qualitative research with pre-defined areas of inquiry [29]. The analytic process will involve familiarization with the notes, followed by the development of a thematic framework based on the predetermined domains. Data will then be indexed using both deductive codes—stemming from the interview guide—and emergent codes that may arise from the content of the notes. A matrix will be constructed to chart responses across cases, enabling systematic cross-case comparisons.

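### Substituting T1 for a missing T0 as baseline pools two time origins in one incidence rate, which can then shift with the share of patients lacking T0

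*Protocol article*

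**What the plan says.** Section 2.4 (Statistical Methods) plans incidence rates per 100 person-years for mood disorders, post-traumatic stress symptoms, reduced quality of life and cognitive impairment. They "will be calculated for participants free of the respective condition at baseline". Cases are defined by score thresholds, beginning with "Incident cases will be defined as follows: a HADS subscale score > 8 for mood disorders (either anxiety or depression subscale").

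The baseline rule is explicit: "Baseline status will be determined using the initial T0 assessment; if T0 data are missing, the T1 (1-month) assessment will be used". The only exclusion for missing baseline data is equally explicit: "Participants with missing data at both T0 and T1 for a given outcome will be excluded from the incidence rate calculation for that outcome".

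For missing data in general, the same section says: "Missing data will be handled using Multiple Imputation by Chained Equations (MICE), assuming a Missing At Random (MAR) mechanism". It adds a sensitivity comparison of complete-case and imputed results.

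On timing, Section 2.1 places T0 "before discharge (or within 15 days post-discharge"), with later visits at 1, 3, 6 and 12 months. Section 2.1.3 says of patients not approached in hospital: "if not, the study management team will contact them within 15 days post-discharge".

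**The concern.** Take two patients who both score above a threshold at 1 month. The first had a negative T0 and is an incident case. The second had no T0, so T1 becomes the baseline; this patient is not free of the condition there and drops out. The same 1-month result is an event in one patient and an exclusion in the other, depending only on whether T0 was done.

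Patients with a T0 are therefore observed for incidence over months 0 to 12, and patients without one over months 1 to 12. If new cases arise at a different pace in the first month home than later, these are two different rates. The pooled figure is a blend of them, weighted by T0 completion, which is a feature of study logistics and not of the patients' illness.

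The planned imputation does not remove this. The explicit T1 fallback and the both-missing exclusion show that baseline status for incidence is not taken from imputed T0 values. The complete-case comparison does not vary the baseline rule either.

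**Working it through.** **Figures in the article.** It gives no incidence rate and no proportion missing T0. Its one sizing figure is reproduced by 350 × 0.80 = 280 patients. Every risk and missing fraction below is an assumption.

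**General form.** Let E and PY be events and person-years with T0 in everyone, E1 and PY1 the parts falling between T0 and T1, and m the share missing T0, at random. Anyone already positive at discharge is assumed still positive at T1. With person-time starting at T1 for patients without T0:

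rate(m) = (E − m·E1) / (PY − m·PY1)

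This does not depend on m only if E1/PY1 = E/PY, that is, if the first-month rate equals the overall rate. A constant hazard is the natural case.

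**Set 1, per patient negative at T0.** 10% become positive at T1. Of the rest, 10% become positive later, spread evenly over the 3-, 6- and 12-month visits (mean 7/12 year).

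- E = 0.10 + 0.90 × 0.10 = 0.19
- PY = 0.10/12 + 0.90 × (0.10 × 7/12 + 0.90) = 0.0083 + 0.8625 = 0.8708
- E1 = 0.10; PY1 = 1/12 = 0.0833
- m = 0: 0.19/0.8708 = 21.8 per 100 person-years
- m = 20%: 0.17/0.8542 = 19.9
- m = 40%: 0.15/0.8375 = 17.9
- m = 100%: 0.09/0.7875 = 11.4

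With 5% positive at T1, 40% missing moves the rate from 15.9 to 14.2. With 15%, it moves from 28.4 to 22.0.

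**Set 2, different onset shapes.** 280 patients, 25% positive at T0 (so 210 at risk), no dropout, events at interval midpoints. Risks are for T0–T1, T1–T2, T2–T3 and T3–T4.

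For risks of 10/5/5/5%:

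- E = 21 + 9.45 + 8.98 + 8.53 = 48.0
- PY = 16.6 + 30.7 + 43.8 + 83.2 = 174.3, so the rate is 27.5
- At m = 20%, 0.20 × 21 = 4.2 cases are lost and the rate is 43.8/170.9 = 25.6

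| Onset pattern | m = 0 | m = 20% | m = 50% |
|---|---|---|---|
| Early, 10/5/5/5% | 27.5 | 25.6 | 22.6 |
| Stronger early, 15/5/5/5% | 34.5 | 31.3 | 26.3 |
| Constant hazard 0.25 per year | 25.0 | 25.0 | 25.0 |
| Late, 1/3/6/12% | 22.8 | 23.0 | 23.3 |

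**If the clock starts at T0 for patients without T0.** They then add a first month in which no event can be counted. At m = 50% the constant-hazard rate falls from 25.0 to 23.8, the 10/5/5/5% rate from 27.5 to 21.5, and the late-onset rate from 22.8 to 22.2.

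**After the fix.** With one origin for everyone and risks of 10/5/5/5%, the rate from T0 in patients with an observed T0 is 27.5 at any m. The rate from T1 in patients negative at T1 is 17.1 at any m. The rule as written gives a value between the two.

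**The case against.** **Leaving out the patient without T0 who is positive at T1 is defensible.** That patient was never shown to be free of the condition and may have been positive at discharge. This stands: counting all such patients as incident would be no remedy. The difficulty is the pooling of two origins.

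**Late entry is a standard device.** With the clock starting at T1 and a constant hazard, nothing moves, and with late onset the rate rises slightly. This also stands. A reader might infer that the pooled rate is always biased downward; the calculations do not support that.

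**The shift is small beside sampling error.** Set 1 assumes 10% in one month and 10% over the next eleven, roughly an elevenfold difference in hazard. With 210 patients at risk it gives about 40 events and an exact 95% interval of about 15.6 to 29.8, which contains both 19.9 and 17.9. That limits the practical weight but does not remove a systematic shift.

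**Missed T0 may be rare.** A reader might infer from the two 15-day statements that T0 will often be missed. The documents do not support this. Section 2.1.3 expects most patients to be approached before discharge and plans twice-weekly reminders to the main sites. Section 2.1 puts over 90% of good-outcome discharges at 11 hospitals, so the centres without a local investigator contribute little. Nothing says that a baseline done shortly after day 15 ceases to count as T0.

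**No planned comparison is distorted.** A reader might also fear misleading differences in incidence between hospitals or modalities. Sections 2.2 and 2.4 compare modalities on recruitment and retention only.

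**Conclusion.** The point holds in a limited form. The rule in Section 2.4 lets first-month onset count only in patients with a T0 and pools them with patients observed from T1. The pooled rate is independent of T0 completion when the hazard is constant and person-time for patients without T0 starts at T1. Otherwise it generally shifts. On the illustrative early-onset assumptions, 20% missing T0 lowers it by about 7% (27.5 to 25.6) to 9% (21.8 to 19.9, and 34.5 to 31.3). With late onset and the clock at T1 it rises by about 1% (22.8 to 23.0). The true size is unknown, because the article gives neither the onset pattern nor the share missing T0, and the calculations take T0 as missing at random.

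Incidence is a secondary descriptive result. Recruitment, retention and the prevalence estimates at each visit, including T1, do not use this rule. The change is worth making because it is cheap, not because a main conclusion is at risk.

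**What to change.** In Section 2.4, give each incidence rate a single time origin:

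- (a) a rate from T0 in participants with an observed T0 who are negative at T0;
- (b) a rate from T1 in all participants negative at T1, whether or not T0 was done, with person-time starting at T1.

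Keep the pooled rate with the T1 fallback only as a sensitivity analysis, and report the number without T0 for each outcome. Eligibility for (b) should not also require a negative T0 where one exists, since inclusion would then again depend on T0 having been done.

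The cost is a few words and an extra column in the incidence table; no new data are needed. Rate (a) omits patients without T0 and has a slightly wider interval. Rate (b) can include patients who were positive at T0 and had recovered by T1, so it should be labelled as becoming positive after a negative 1-month result.

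Separately, reconcile Sections 2.1 and 2.1.3 on whether the 15-day limit refers to contact with the patient or to the completed T0 assessment.
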